### Data collection and patient follow-up

At the time of patient consent for participation in the trial and prior to randomization, baseline patient characteristics will be recorded. These will mainly comprise demographics (age, sex, BMI) and past medical history, including comorbidities for the assessment of performance status. Clinical presentation will also be documented with a focus on patient symptoms and signs; in cases of solid tumors, imaging data will also be collected and evaluated: tumor size and staging, vessel involvement, and pancreatic duct (PD) diameter, as well as the presence of preoperative biliary drainage and treatment with somatostatin analogs. At the time of surgery, the pancreatic texture will be documented (soft versus hard gland) and the PD diameter will be also measured. Previously discussed minor variations in operative approach and anastomotic reconstruction will be added in patient record forms. Regarding the quality of life assessment, patients will complete the latest translated version of the EuroQoL EQ-5D-5 L questionnaire, which is a self-reported assay focusing on five parameters: pain/discomfort, anxiety/depression, usual activities, self-care, and mobility. Each of these parameters is scored from 0 to 5 (no issue, slight problem, moderate problem, severe problem, unable). Patients also score independently their health status on a scale numbered from 0 to 100: 100 meaning the best health they can imagine, and 0 the worst. The questionnaires will be filled and collected by medical or nursing staff on postoperative days 1, 3, 5, and 7 during the patients’ hospital stay; further questionnaires will be completed in the postoperative setting every week until day 30, every month until day 90, and every 3 months until 12 months, when the evaluation will terminate (Fig. 3). Remote completion will take place via telephone communication, by mail, or face-to-face for all patients who are followed up at the participating centers. Furthermore, in the postoperative setting, primary and secondary outcomes during the hospital stay will be documented daily by the trial coordinators. Patients will be further followed up after discharge with out-patient clinic appointments or via telephone/video conference as an alternative to monitor for delayed postoperative complications, quality of life changes, and disease recurrence patterns. Frequent communication and close monitoring of enrolled patients by the participating centers via telephone and mail will aim to promote patient retention during the trial period. All collected data are de-identified and stored safely in a centralized online database, which is accessible by all participating institutions for data input. The stored data are not available to individual collaborators and are only screened by two dedicated members of the trial team for assessment of wrong or missing data. Data processing regarding the results is conducted by a group of two independent statisticians who work under the data monitoring committee.

**Fig. 3 Fig3:**
[figure not shown]
Timeline diagram of the studied primary and secondary outcomes. EQ-5D-5L, Quality of Life Questionnaire; POD, postoperative day; PDAC, pancreatic adenocarcinoma

### Statistical considerations and analysis

The main hypothesis in the PORTAL trial is that functional recovery of patients who undergo RPD is non-inferior to the one of patients who undergo OPD. Based on institutional historical data and information from retrospective series in the literature, the time to functional recovery in OPD is 10 days with a standard deviation of 2.5 days. Non-inferiority of functional recovery in RPD will be assessed with a non-inferiority (*δ*) margin of 10% or 1 day. With a one-sided test, a significance level of 5% (*α* = 0.05), and a power (1 − *β*) of 80%, the cohort for the trial is calculated to 200 patients (per-protocol (PP) group), using the PASS 11.0 software (NCSS, Kaysville, UT, USA) with a sample allocation ratio of 1:1 between the RPD and OPD groups. However, we anticipate a conversion rate in the RPD group of 10%, 3% incidence of occult abdominal metastatic disease in both groups, and 5% of patients to be lost to follow-up. Therefore, the final cohort will include 122 patients in each arm (intention-to-treat (ITT), Fig. 1). The main analysis will be conducted on the ITT group according to the randomized initial assignment of patients in each study arm at baseline. All enrolled patients from the ITT population who do not fulfill the aforementioned protocol violations will be included in the PP group. Additionally, patient characteristics of those who will be excluded from the PP analysis will be separately evaluated. Non-inferiority will be concluded if the lower bound of the 95% confidence interval (CI) for the difference between the two groups in time to functional recovery is not lower than − 1 day of the non-inferiority margin.

A second primary endpoint of the study is the percentage of patients with a diagnosis of pancreatic adenocarcinoma in each study arm, who will be fit for the initiation of postoperative adjuvant chemotherapy 8 weeks after the day of surgery. Institutional empirical data demonstrate that 50% and 75% of patients who undergo OPD and RPD, respectively, are eligible for adjuvant chemotherapy at 8 weeks, which is considered the optimal time for postoperative systemic treatment. With the same power and significance level as in the ITT group, 64 patients with pancreatic adenocarcinoma will be included in each arm to assess for the superiority of RPD.

Primary and secondary outcome data for both ITT and PP groups will be compared utilizing appropriate statistical methodology. Categorical variables will be represented as frequency and proportion and will be analyzed using Fisher’s exact or chi-square tests, as appropriate. Continuous variables will be presented as mean values with standard deviation (SD), or median values with interquartile range (IQR), and will be compared using the two-sample *t*-test or Mann-Whitney *U* test, as per the type of distribution. A logistic regression analysis was performed for consideration of randomization stratification, based on the predetermined parameters. Survival of patients with pancreatic adenocarcinoma between the two arms will be estimated using the Kaplan-Meier analysis method and compared between the groups with the log-rank test. The SAS software v. 9.2 (SAS Institute Inc., USA) was utilized for all statistical analyses.

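### The stated one-sided 5% level conflicts with the 95% CI decision rule and does not produce either sample size; 200 in total and 64 per arm both fit one-sided 2.5%

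*Protocol article*

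**What the plan says.** All the statements stand in the protocol article, in the section Statistical considerations and analysis.

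- Level: "With a one-sided test, a significance level of 5" per cent.
- Planning values: "the time to functional recovery in OPD is 10 days with a standard deviation of 2.5 days", with a "margin of 10% or 1 day".
- Resulting size: "the cohort for the trial is calculated to 200 patients", labelled as the per-protocol group, with 80% power and 1:1 allocation. Attrition of 10%, 3% and 5% then takes this to 122 per arm.
- Decision rule: non-inferiority is concluded if the "lower bound of the 95% confidence interval (CI") does not fall below −1 day.
- Second primary endpoint, with 50% expected after open and 75% after robotic surgery: "With the same power and significance level as in the ITT group, 64 patients with pancreatic adenocarcinoma will be included in each arm". The purpose here is superiority.

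The paragraph on analysis methods in the same section names Fisher's exact or chi-square tests for categorical outcomes, and the t-test or Mann-Whitney test for continuous ones.

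**The concern.** One bound of an ordinary two-sided 95% confidence interval is a one-sided test at 2.5%. A one-sided test at 5% corresponds to a 90% interval. The article therefore gives two different type I error rates for its main confirmatory claim.

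If the stated level governs, the chance of declaring non-inferiority when robotic surgery is truly one day slower is 5%. If the interval rule governs, it is 2.5%. A result that falls between the two bounds would be non-inferior under one statement and not under the other, and nothing in the text says which prevails. The second primary endpoint inherits the ambiguity because it borrows the same level. In addition, a reader who enters the stated inputs in the standard formulas gets neither 200 nor 64 per arm.

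**Working it through.** **Inputs.** From the statistical section: SD 2.5 days, margin 1 day, power 80%, 1:1 allocation; 50% v 75% for chemotherapy. Assumption: a true difference in recovery time of 0. The article states none, and 0 is the usual planning value for a non-inferiority aim.

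**1. Functional recovery, normal formula.** n per arm = 2 × SD² × (z₁₋α + z₀.₈₀)² / margin².

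- One-sided 5%: 2 × 6.25 × (1.645 + 0.842)² / 1 = 77.3, so 78 per arm, 156 in total.
- One-sided 2.5%: 2 × 6.25 × (1.960 + 0.842)² / 1 = 98.1, so 99 per arm, 198 in total.

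**2. Functional recovery, t-test power (noncentral t).**

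| Level | Smallest n per arm for 80% power | Power at 100 per arm |
|---|---|---|
| One-sided 5% | 78 | 88.0% |
| One-sided 2.5% | 100 | 80.4% |

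The plan's 200 is reproduced exactly at one-sided 2.5% and not at the stated 5%. Against 156, the stated figure is 200/156 = 1.28 times as large.

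**3. Could something else explain 200 at one-sided 5%?**

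- Mann-Whitney instead of the t-test: 81 per arm for normal data, 90 in the least favourable case. Neither is 100.
- Attrition: no. The 200 is already the per-protocol figure and attrition is added afterwards: 100 / (1 − 0.18) = 122 per arm, which agrees with the article.
- Other planning values: an SD of about 2.83 days, or a true difference of about 0.12 day against the robotic arm, would give 80% power at 100 per arm. The article states an SD of 2.5 and no such difference.

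**4. Where the two rules disagree.** With 100 per arm and SD 2.5, the standard error is 2.5 × √(2/100) = 0.354 day. The distance from the estimate to the bound is 0.58 day for a 90% interval and 0.70 day for a 95% interval. Non-inferiority is declared if the robotic arm is observed to be slower by up to 1 − 0.58 = 0.42 day under the first, and up to 1 − 0.70 = 0.30 day under the second. An observed excess of 0.30 to 0.42 day is decided differently by the two statements.

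**5. Chemotherapy within 8 weeks, 50% v 75%.** Pooled formula: n = [z₁₋α √(2 × 0.625 × 0.375) + z₀.₈₀ √(0.25 + 0.1875)]² / 0.25². Fisher power is by enumeration of all tables.

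| Method | One-sided 5% | One-sided 2.5% (two-sided 5%) |
|---|---|---|
| Pooled chi-square | 45.3, so 46 | 57.7, so 58 |
| With continuity correction | 53.0, so 54 | 65.4, so 66 |
| Fisher's exact | 54 | 64 (80.2%; 63 gives 79.4%) |
| Fisher power at 64 per arm | 87.6% | 80.2% |
| Chi-square power at 64 per arm, exact | 90.8% | 84.9% |

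No standard test at the stated level, without an added allowance for attrition, needs 64 per arm. Fisher's exact test at two-sided 5% needs exactly 64.

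**The case against.** Four points can be made for the plan.

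- **The interval is not called two-sided.** Read as a one-sided 95% bound, it agrees with a one-sided 5% test. This is possible but is not the ordinary meaning of a 95% confidence interval, the text does not say it, and it leaves 200 unexplained.
- **The zero true difference is not stated.** So the 156 is conditional, and the full protocol may list other software inputs. That stands as a caveat. Even so, zero together with one-sided 2.5% gives exactly the published 100 per arm, without any unstated value.
- **The match for 64 depends on the test.** Chi-square gives 58 and the continuity-corrected formula 66 at two-sided 5%. Other routes come close: 53.0/0.82 = 64.6 (one-sided 5%, continuity correction, 18% attrition) or 57.7/0.9 = 64.1 (two-sided chi-square, 10% loss). This stands. The article mentions no attrition allowance for this endpoint, so 64 supports the conclusion but does not prove the level by itself.
- **The trial is not underpowered, and the decision rule is explicit.** Both are true. An analyst who follows the written rule literally would not use a 90% interval. But a stated significance level is also a rule, and the two cannot both hold.

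**Conclusion.** The concern holds. The declared one-sided 5% disagrees with the 95% interval rule on its ordinary two-sided reading. It also disagrees with the size of 200 (156 needed, given a zero true difference) and with the 64 per arm (46 to 54 needed). The interval rule and the size of 200 both point to one-sided 2.5%, and the 64 agrees if Fisher's exact test was used. The stated level is therefore the likely error.

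The consequence is a type I error for the main claim of either 5% or 2.5%, and a band of observed results, about 0.30 to 0.42 day at 100 per arm, on which the two statements give opposite conclusions. Enrolment is adequate either way: power for functional recovery at 100 per arm is 88.0% or 80.4%. Because this is the error rate of a primary confirmatory test, it must be corrected. It is a contradiction in what the article fixes, not a detail that could be left to a separate analysis plan.

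**What to change.** - For functional recovery, replace the one-sided 5% level with one-sided 2.5%, stated as equivalent to a bound of the two-sided 95% confidence interval. State that the true difference was taken as zero, if that is so.
- For chemotherapy, replace the reference to the same significance level with two-sided 5%. Name the test behind the 64 per arm (Fisher's exact reproduces it), and say whether 64 is before or after attrition.
- Leave 200, 122 per arm (244 in total) and 64 per arm as they are.

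No patients are added and no procedure changes. The sponsor commits to the stricter level that the interval rule and the size of 200 already imply. Because recruitment began in September 2020 and the change restates the type I error of primary endpoints, it should be made as a dated amendment, without reference to outcome data. It should go through the ethics route that the article's monitoring section sets for major modifications, if it is classed as one.

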### Secondary outcome measures (Tables 1 and 2)

Multiple secondary outcomes will be compared within the trial. Intraoperative parameters will include operative time (from the first incision to skin closure) and estimated blood loss. Additionally, pathologic characteristics will also be studied, including tumor size and degree of differentiation, presence of perineural and/or lymphovascular invasion in PDAC, resection margin status, and number of harvested and infiltrated regional lymph nodes, as defined by the 8th edition of the American Joint Committee for Cancer [19]. Regarding the resection margin (R), it will be defined as R0 when tumor cells are detected > 1 mm from the margin, R1 when they are detected ≤ 1 mm from the margin, and R2 when there is macroscopically margin positivity. In the postoperative setting, the main secondary outcomes are complication rates as defined by the Clavien-Dindo classification [20] within 30 days and mortality within 90 days from operation. The trial will assess the occurrence of postoperative pancreatic fistula, biliary leak, chyle leak, delayed gastric emptying, bleeding, and surgical site infections (SSI) in both arms as defined by the International Study Group on Pancreatic Surgery [21–24] and the International Study Group in Liver Surgery [25], with a specific focus on the severe complications (Clavien-Dindo grade IIIa and higher). Subsequently, re-intervention (radiological, endoscopic, or surgical) and readmission rates will also be assessed. All interventions necessary for the treatment of participating patients in terms of management of potential complications are allowed. There are no limitations regarding patients’ care within this trial. All performed interventions will be documented in detail and assessed accordingly. Perioperative costs including postoperative hospitalization and readmissions within 30 days from the surgery will also be documented and evaluated. Lastly, quality of life (QoL) measurements will occur using patient questionnaires up to 3 months after surgery.

**Table 1 Tab1:** Trial progression portrayed as per Standard Protocol Items: Recommendation for Interventional Trials (SPIRIT) guidelines

Event	Preoperative setting (3 to 14 days pre-op)	Day of surgery	POD 1	POD 2	POD 3	POD 5	POD8/discharge day	POD 14	POD 30	POD 90	6 months post-op	1 year post-op	2 years post-op/time of death
Eligibility screening	X												
Informed consent	X												
Baseline characteristics	X												

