***Variable***	
**Primary outcomes** Time to functional recovery, *n* (days) Patients with PDAC who start adjuvant chemotherapy at 8 weeks, *n* (%)	
**Secondary outcomes** Estimated blood loss, ml Operative time, min Length of hospital stay, days 30-day morbidity, *n* (%) < Clavien-Dindo grade IIIa ≥ Clavien-Dindo grade IIIb 30-day mortality, *n* (%) 90-day mortality, *n* (%) 30-day readmission, *n* (%) Reoperation, *n* (%) Quality of life assessment Perioperative costs, $ In PDAC Resection margin status, *n* (%) Harvested lymph nodes, *n* Positive lymph nodes, *n* Recurrence, *n* (%) Recurrence site, *n* (%) Recurrence-free survival, month*s* Overall survival, months	

*OPD* open pancreaticoduodenectomy, *RPD* robotic pancreaticoduodenectomy, *PDAC* pancreatic adenocarcinoma

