The second primary endpoint of this study is the timing of adjuvant chemotherapy initiation in patients with pancreatic adenocarcinoma, who represent the main bulk of pancreatoduodenectomies. The role of chemotherapy in PDAC has been long established, and different regimens have been identified to provide survival benefits [43, 44]. A recent retrospective study by Girgis et al. demonstrated that long-term oncological outcomes in patients with PDAC who undergo RPD are borderline superior compared to the open approach [45]. These results differentiate from a large study on cervical carcinoma that showed inferior overall survival in the minimally invasive group [46]. Thus far, no prospective data exist to support non-inferiority of RPD regarding oncological outcomes. The optimal time for chemotherapy treatment in the postoperative setting in PDAC has been identified to be no later than 12 weeks in order to achieve a combination effect of local and systemic treatments, yet most oncologists aim to start at 8 weeks [47]. Based on institutional data, we identified the percentage of patients who initiate adjuvant chemotherapy to be approximately 50% in OPD and 75% in RPD, and we aim to compare the two groups and assess for the superiority of RPD (64 patients in each arm). Furthermore, we will compare the recurrence-free survival and overall survival between the two groups, as well as the patterns of recurrence which are closely associated with long-term outcomes in PDAC [48].

Secondary endpoints of the PORTAL trial include perioperative and long-term outcomes. A recent meta-analysis [27] and smaller retrospective series within the past few years have demonstrated significantly lower overall complication rates in RPD compared to the open approach, as well as benefits in terms of estimated intraoperative blood loss. Additionally, retrospective data on RPD in PDAC patients have shown increased R0 resection rates and higher numbers of harvested lymph nodes [27, 49] and no difference in recurrence-free and overall survival [50]. The targeted analysis of PDAC patients within the PORTAL trial will be able to answer the question of long-term oncological outcomes in RPD. Moreover, a comprehensive cost analysis will include and compare operative charges, postoperative institutional expenses, and potential readmission costs to identify in detail the presence—or lack thereof—of the economic burden of robotics utilization in pancreatoduodenectomy [51].

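### The rule that picks the test by distribution is applied to perioperative cost without exception; if costs are skewed it points to a rank test, which does not estimate the mean cost behind the economic-burden question

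*Protocol article*

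**What the plan says.** Table 2 lists "Perioperative costs", in dollars, among the secondary outcomes. The section on secondary outcome measures gives the content: "Perioperative costs including postoperative hospitalization and readmissions within 30 days from the surgery will also be documented and evaluated".

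The analysis is described in Methods, Statistical considerations and analysis. The scope is stated first: "Primary and secondary outcome data for both ITT and PP groups will be compared utilizing appropriate statistical methodology". For continuous variables the summary is either of two: "Continuous variables will be presented as mean values with standard deviation (SD), or median values with interquartile range (IQR"). The variables "will be compared using the two-sample *t*-test or Mann-Whitney *U* test, as per the type of distribution". No exception is made for cost, and no mean cost difference, confidence interval or cost model is named.

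The Discussion states the purpose. It announces that "a comprehensive cost analysis will include and compare operative charges, postoperative institutional expenses, and potential readmission costs", in order to identify the presence or absence "of the economic burden of robotics utilization in pancreatoduodenectomy".

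**The concern.** Economic burden is a question about total spend, and total spend is mean cost times number of patients. The quantity of interest is therefore the difference in arithmetic mean cost, whatever the shape of the data. The stated rule instead lets the observed distribution decide which quantity is compared.

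Costs that include hospital stay and readmissions usually have a long right tail. If they do here, the rule points to medians with Mann-Whitney. A rank test uses only the ordering of costs, so it gives little weight to how expensive the most expensive patients are. That matters when the arms differ in shape. The Background refers to the significant costs of the robotic platform, and the Discussion cites retrospective evidence of fewer complications with the robotic approach. A higher floor with a thinner tail is the pattern in which ranks and means can disagree. The trial could then report a robotic cost burden where average spend is the same.

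**Working it through.** **No figure to reproduce.** The article gives no cost mean, SD, effect or power. The size of the problem can only be illustrated, and every cost input below is an assumption. The one input from the document is 122 patients per arm (Statistical considerations and analysis).

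**Model.** Cost = base cost + complication cost, in relative units. Base cost is lognormal with a chosen coefficient of variation (CV). A complication occurs with probability p and costs a gamma-distributed amount (shape 2, mean 100). Mean cost = base + p × 100. Tests are two-sided at 5%, so the nominal rate of falsely calling robotic dearer is 2.5%.

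**Equal means, larger offset.**
- Open: 100 + 0.25 × 100 = 125.
- Robotic: 110 + 0.15 × 100 = 125.
- Mann-Whitney significant with robotic dearer: about 27% of trials at base-cost CV 0.2, 11% at 0.3, 6% at 0.4 and 5% at 0.5.
- At CV 0.2 the difference in sample medians averages about +6.4 although the means are equal. Welch's t-test on the means rejects in about 5%, both directions together.

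**Equal means, smaller offset.**
- Open: 125 as before. Robotic: 105 + 0.20 × 100 = 125.
- Mann-Whitney significant with robotic dearer: about 9% at CV 0.2, 4% at 0.4 and 3% at 0.5.

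**Identical cost distributions.** With the same lognormal cost in both arms (log-SD 0.5), Mann-Whitney rejects in 5.1% in total and in 2.5% with robotic dearer. The excess therefore comes from a difference in shape, not from skewness alone.

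**A second cost model.** Lognormal costs with log-SD 0.6, equal means of 100, and 20 or 30 of the robotic mean being a fixed component: Mann-Whitney with a higher robotic median in 13% and 25%, Welch about 5% in total.

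**The error can also run the other way.** With log-SD 0.4 (open) and 0.7 (robotic) and a robotic mean truly 15% higher, Mann-Whitney reports higher robotic cost in about 1% of trials and Welch in about 36%.

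**A true saving.**
- Open: 100 + 0.30 × 100 = 130.
- Robotic: 108 + 0.15 × 100 = 123, a saving of 7.
- At CV 0.2, Mann-Whitney finds the saving in about 2% of trials, and the median difference has the wrong sign (about +1.7). Welch finds it in only about 15%.

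**The case against.** The strongest reply is that the article does not send cost to Mann-Whitney. It offers two tests, chosen "as per the type of distribution", and names no normality test or threshold. With 122 per arm an analyst could use the t-test on means within this wording. It also nowhere says that costs are skewed. Both points stand, so selection of the rank test is likely, not certain.

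A second reply is that a condensed article may leave the cost method to a statistical analysis plan or a health-economic plan that is not shown. That would answer a complaint about missing detail. It does not answer this one, because the printed rule covers primary and secondary outcomes and cost falls under it.

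Third, the size depends heavily on the inputs. The 27% needs a base-cost CV of 0.2 and the larger offset. A CV that low is not supported for seven centres and mixed benign and malignant disease. The Background also describes specific robotic complication rates as comparable to open surgery, which would weaken the difference in shape. This stands, and it is why a range is given.

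A reader might infer that the rule will certainly select Mann-Whitney, or that the cost question will be answered wrongly. The document supports neither. Nothing in it prevents mean costs from being reported as well. In the true-saving example the mean comparison also misses the saving in about 85% of trials (100% − 15%), so low power is not a fault of the rank test alone.

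**Conclusion.** The point holds in a conditional form. The stated rule makes the cost comparison depend on the observed distribution, while the Discussion asks a question that depends on the mean. If costs are right-skewed, the rule points to a test that does not estimate mean cost per patient. If the arms also differ in shape, that test can signal a robotic burden at equal mean cost, in roughly 3% to 27% of trials over the assumed inputs, against a nominal 2.5%.

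This rests on four assumptions that the document does not settle: costs are skewed; the analyst follows the rule to the rank test; the fixed robotic cost is counted in the operative charges; and robotic surgery thins the expensive tail. Without a difference in shape there is no excess. The consequence is limited to one secondary outcome. Neither primary endpoint, the sample size nor the safety monitoring is touched. It is still worth correcting, because the mismatch is in the stated method and the remedy is cheap.

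**What to change.** Exempt cost from the distribution rule, in the analysis section or the statistical analysis plan. Suggested wording: *Perioperative cost will be compared as the difference in arithmetic mean cost per randomised patient (intention-to-treat), with a 95% confidence interval from a non-parametric bootstrap, Welch's method or a generalised linear model, irrespective of the distribution. Medians and interquartile ranges are descriptive only.* If a separate plan already says this, a reference to it is enough.

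This costs one sentence, needs no new data and leaves the other outcomes unchanged. The downside is that the interval may be wide, and power to detect a modest saving stays low (about 15% in the example above), so a non-significant result should not be read as evidence of no burden.

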Arm allocation	X												
QoL questionnaire (EQ-5D-5 L)	X						X	X	X	X	X	X	
Intraoperative outcomes		X											
Postoperative outcomes/secondary endpoints			X	X	X	X	X	X	X	X			
Primary endpoint assessment							X			X			
Recurrence-free and overall survival assessment													X

*pre-op* preoperative, *post-op* postoperative, *POD* postoperative day, *QoL* quality of life

**Table 2 Tab2:** Primary and secondary outcomes of the PORTAL trial

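### Adjusting EQ-5D-5L comparisons for the scheduled preoperative score would be a free improvement on the unadjusted two-sample tests that the general analysis rule prescribes

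*Protocol article*

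**What the plan says.** All references are to the protocol article.

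- **Baseline.** Table 1 marks the EQ-5D-5L in its first column, 3 to 14 days before surgery. It marks it again at postoperative day (POD) 8 or discharge, POD 14, POD 30, POD 90, 6 months and 1 year.
- **Outcome.** Table 2 includes "Quality of life assessment" among the secondary outcomes. Data collection and patient follow-up describes the five dimensions and adds a numeric scale: "Patients also score independently their health status on a scale numbered from 0 to 100".
- **Analysis.** Statistical considerations and analysis sets one rule for all outcomes: "Primary and secondary outcome data for both ITT and PP groups will be compared utilizing appropriate statistical methodology". It then says what that methodology is. Categorical variables go to Fisher's exact or chi-square tests, and continuous variables "will be compared using the two-sample *t*-test or Mann-Whitney *U* test, as per the type of distribution".
- **Adjustment.** The only adjusted model named is this one: "A logistic regression analysis was performed for consideration of randomization stratification, based on the predetermined parameters". The stratification parameters, given under Randomization process, are fistula risk, endoscopic biliary stenting and a diagnosis of pancreatic adenocarcinoma. Baseline quality of life is not among them, and logistic regression does not suit a continuous score.

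No section names a baseline covariate, a change score, ANCOVA or a repeated-measures model for the EQ-5D-5L.

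**The concern.** A preoperative score usually predicts the later score of the same patient. A two-sample test of follow-up scores treats that predictable part as noise. It also makes no correction if one arm happens to start in better health. Patients range from those with cystic lesions or chronic pancreatitis to those with pancreatic cancer, some of them stented, so real differences in preoperative health are plausible, although the article gives no figure for them.

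At stake is the precision of a secondary comparison that readers will probably set beside the primary result, because the Discussion links functional recovery to patient-reported quality of life. The baseline is already on the schedule, so leaving it out of the analysis gives up information at no saving.

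**Working it through.** **Inputs from the article.** There are 122 patients per arm by intention to treat, allocated 1:1. The article's own inflation reproduces: 100 per arm / (1 - 0.10 - 0.03 - 0.05) = 100 / 0.82 = 121.95, rounded up to 122. It also expects 5% loss to follow-up, and 122 x 0.95 = 115.9, so about 116 per arm would supply follow-up scores. It states no SD, effect, power or correlation for the EQ-5D-5L, so there is no quality-of-life figure to reproduce.

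**Assumptions.** Rho, the correlation between preoperative and follow-up score, is varied from 0.2 to 0.6. The unadjusted comparison starts at 80% power with a two-sided 5% test. The formulas are large-sample ones for the t-test. The Mann-Whitney option is equally without a baseline term.

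**Formulas.** With the SD of the follow-up score set to 1:

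- Variance of the arm difference relative to the unadjusted test: 1 - rho² for ANCOVA, and 2(1 - rho) for a test on change scores.
- Detectable difference at 80% power: (1.96 + 0.8416) x sqrt(2/116) x sqrt(1 - rho²) = 0.368 x sqrt(1 - rho²).
- Power after adjustment: Phi(2.8016 / sqrt(1 - rho²) - 1.96).

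| rho | ANCOVA variance | Change-score variance | Detectable difference, 116 per arm (SD) | Power, ANCOVA |
|---|---|---|---|---|
| 0 | 1.00 | 2.00 | 0.368 | 80.0% |
| 0.2 | 0.96 | 1.60 | 0.360 | 81.6% |
| 0.3 | 0.91 | 1.40 | 0.351 | 83.6% |
| 0.4 | 0.84 | 1.20 | 0.337 | 86.4% |
| 0.5 | 0.75 | 1.00 | 0.319 | 89.9% |
| 0.6 | 0.64 | 0.80 | 0.294 | 93.8% |

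Worked example at rho 0.5: 2.8016 / 0.8660 = 3.235; 3.235 - 1.96 = 1.275; Phi(1.275) = 0.899. The variance falls by 25%, which is worth 1 / 0.75 = 1.33 times the patients. With all 122 per arm the detectable difference goes from 0.359 to 0.311 SD. If the one-sided 5% level of the primary test were used instead, the power at rho 0.5 would be Phi(2.4865 / 0.8660 - 1.645) = Phi(1.226) = 0.890, so the picture does not depend on sidedness.

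**Chance imbalance.** At 122 per arm the standard error of the baseline difference is sqrt(2/122) = 0.128 SD. A difference of 1.96 standard errors is 0.251 SD, and rho x 0.251 of it carries into the follow-up comparison: 0.075 SD at rho 0.3 and 0.125 SD at rho 0.5. Given such a draw, the standardized follow-up difference under no effect has mean 1.96 x rho and variance 1 - rho². The chance of exceeding 1.96 in absolute value is then about 8% at rho 0.3 and 13% at rho 0.5. Averaged over all draws it is 5%. These conditional figures ignore stratification and describe a deliberately extreme draw.

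**The case against.** The strongest reply is that the sentence is generic. It assigns a default test to each type of variable, never mentions quality of life, and comes from a condensed article whose full protocol and analysis plan are not shown. The model for a repeated patient-reported outcome is commonly settled there. A two-sample test could also be run on change from baseline, which would use the preoperative score, and the article does speak of following changes in quality of life.

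Part of this stands. The EQ-5D-5L is reached only through the general rule, and the ordinal dimension levels may fall under the chi-square or Fisher rule instead. The preoperative measurement rests on Table 1, because the questionnaire timetable in Data collection and patient follow-up gives postoperative times only. But the article does state a test for continuous secondary outcomes, so this is a stated method that can be improved, not a gap. The change-score reading is not written in the analysis section. Even if it were meant, a change score is less precise than ANCOVA at every rho in the table, and less precise than the plain follow-up comparison when rho is below 0.5.

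The design also does some of the work already. Randomization is stratified on pancreatic adenocarcinoma and biliary stenting, which bear directly on preoperative health, and entry is limited to performance status 0 or 1. Stratification therefore limits the imbalance described above, though it does not remove differences within strata.

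A reader might infer that the planned comparison is biased or has an inflated error rate. The documents do not support that: a randomized two-sample comparison is unbiased and keeps its 5% error over randomization. A reader might also infer, from the Discussion, that the primary endpoint is touched. It is not. Primary outcome measures defines functional recovery by four clinical criteria, none of which uses the EQ-5D-5L.

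**Conclusion.** The point holds as a free improvement. The general rule compares the 0-100 health score between arms without the preoperative value that Table 1 schedules. The cost is precision, together with whatever chance baseline difference stratification leaves behind. It is not an error of validity, and the primary conclusions do not change.

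The size rests on an assumed correlation and an assumed 80% starting power for an outcome that the trial does not power. The gain is under 2 percentage points of power at rho 0.2, passes 5 points between rho 0.3 and 0.4, and reaches about 14 points at rho 0.6. Correlations are probably lower in the first postoperative weeks than at 3 to 12 months, so the early visits should be expected to gain least.

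**What to change.** In Statistical considerations and analysis, add a sentence to this effect: the EQ-5D-5L 0-100 score, and the index if one is derived, will be compared between arms by ANCOVA at each visit, or by a repeated-measures model with arm-by-visit terms, with the preoperative score and the three stratification factors as covariates; the adjusted difference will be reported with its 95% CI. Choose one of the two models and fix it before results by arm are seen, so that adjusted and unadjusted results cannot be chosen between afterwards.

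Two small checks go with it. Mention the preoperative questionnaire in Data collection and patient follow-up, so that the text agrees with Table 1. Settle one list of visits for the model, because the postoperative questionnaire days in that section differ from those in Table 1.

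The cost is wording only. No extra patients, visits or measurements are needed.
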